Parental Stress Index (PSI)	The PSI (29, 30) is a self-administered questionnaire assessing difficulties faced by parents of children aged 0 to 10 years in their parental role. The PSI measures perceived parenting stress. It is a 5-point Likert-type scale including 120 items on two domains: the child and parent characteristics domain (101 items, 47 and 54 items in the child and parent domain, respectively). Its validation and reliability have been substantiated. It is recommended as a screening and interpretive tool for evaluating the state of the parenting system as it is perceived by the parent. Its aim is to offer interpretive guidelines to help identify issues that may lead to problems in the child’s or parent’s behavior that may aggravate parenting. As such, PSI scores are not to be used as a diagnostic tool, but rather as working hypotheses that health professionals may use to assist individual parents. The instrument consists of a Child Domain with 6 subscales (Distractibility/Hyperactivity, Adaptability, Reinforces Parent, Demandingness, Mood, and Acceptability) and a Parent Domain with 7 subscales (Competence, Isolation, Attachment, Health, Role Restriction, Depression, and Spouse/Parenting partner relationship). Each of these stressors represents a sub-scale on which the higher the value, the higher the stress. The different sub-scales provide good internal consistency, as well as good temporal stability (30, 31).
Perinatal Post-Traumatic Stress Disorder (PTSD) Questionnaire (PPQ)	The PPQ (32) is a 14-item self-administered questionnaire specially designed for parents of high-risk perinatal children. Mothers answer either yes or no to each of the 14 items that form the three elements of PTSD: intrusive memories, avoidance behaviors, and symptoms of hyperarousal. The score range is from 0 to 42. A score higher than 6 may be considered as high risk for a PTSD diagnosis according to the DSM-IV (17,19).

*AMMI, Attachment Multiple Model Interview; PSI, Parental Stress Index; PPQ, Perinatal Post-Traumatic Stress Disorder Questionnaire; LIFT, Longitudinal study of preterm infants in the Pays de la Loire region of France; ASQ, Ages and Stages Questionnaires; SDQ, Strength and Difficulties Questionnaire; GSA, Global School Adaptation.*

**TABLE 3 T3:** Outcome measures.

Objectives	Outcomes measures and timepoint(s) of evaluation

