**FIGURE 2 F2:**
[figure not shown]
Study flow chart.

A total of 83 children are considered as eligible for inclusion in the two centers and will be screened for study recruitment. Participation will be offered to the parents (or the legal guardians). Assuming the occurrence of a non-participation rate in the study (due to refusal or for another reason) and an incomplete data rate for an estimated total of 25% of the eligible sample, the number of children with complete analyzable data is estimated at 63 in total. This aligns with the desired sample sizes recommended for pilot studies reported in the literature (33, 34). Participation will be offered to the parents (or the legal guardians) of 83 children considered eligible for inclusion. Consistent with the exploratory nature of this pilot study, we did not perform a statistical power analysis. Power calculations are beyond the scope of a pilot study (35). We will use a confidence interval approach to interpret the results (36). After taking into account exclusion criteria, a total number of 81 children will be included in the study.

Statistical analysis design: A flow chart will be used to depict the screening and inclusion of children included in the analysis. A descriptive analysis of the characteristics of the children included in the study will be carried out.

Descriptive analyses will be presented for all of the data collected about the children included in the study, as well as the data relating to the parents. The qualitative variables will be studied in terms of frequency and percentage. Quantitative variables will be analyzed in terms of absolute scores, medians, interquartile ranges (or extreme values), averages, standard deviations, and/or 95% average confidence intervals.

For each Q-sort score derived from the ASCT (secure, deactivating, hyperactivating, and disorganized), the average of each score recorded at 3 years and again at 5 years will be used to describe children’s attachment representations within the population of children born extremely prematurely (27).

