The analysis will take place on an exploratory basis by studying the factors associated with the children’s attachment representations at 3 and 5 years old. The factors associated with each Q-score will be studied using a univariate linear regression model. A separate model will be performed for each Q-score. Multivariate analyses will be also carried out on an exploratory basis (one multivariate model for each Q-score). The following different factors will be considered (37), including specifically: neurocognitive development (using the score from the GSA questionnaire as an absolute value and the score from the ASQ questionnaire expressed as a score <285 or not); behavioral development (SDQ score between 17 and 40 or not); perinatal, prenatal, and socioenvironmental factors (term of pregnancy, birth weight and length as a z-score, sex, age of the mother, gravidity, parity); comorbidity at birth (composite criterion used in the context of the LIFT follow-up: bronchopulmonary dysplasia at 36 WG, grade 3-4 intraventricular hemorrhage, periventricular leukomalacia, grade 2-3 necrotizing enterocolitis, ligature of ductus arteriosus); the socioeconomic status and level of education of the parents; the use of medically assisted reproduction; the parents’ marital status (separated or not). The following factors will also be taken into account: parental posttraumatic stress, using the score from the PPQ questionnaire (score greater than or equal to 6), and parental stress using the PSI score as an absolute value, as well as the results of the assessment for maternal attachment representations using the scores from the AMMI dimensions as absolute values. An additional analysis using mixed models will also be performed for exploratory purposes (linear models) to analyze the longitudinal aspects of the follow-up of the children included in the study. As described previously, a separate model will be performed for each Q-score.

All tests will be performed with a two-sided level of significance of 0.05.

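### The PPQ post-traumatic stress factor is not consistently defined: the cut-off differs between Table 2 and the analysis section, and the stated 0–42 range does not fit 14 yes/no items

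*Protocol article*

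**What the plan says.** The PPQ is described in two places in the protocol article.

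- **Table 2 (assessment tools).** The instrument has 14 items. On the response format: "Mothers answer either yes or no to each of the 14 items". On the score: "The score range is from 0 to 42". On interpretation: "A score higher than 6 may be considered as high risk for a PTSD diagnosis according to the DSM-IV".
- **Statistical analysis design.** Among the factors considered for each ASCT Q-score: "parental posttraumatic stress, using the score from the PPQ questionnaire (score greater than or equal to 6". The PPQ enters only as this dichotomy. In the same paragraph, the PSI score and the AMMI dimension scores enter as absolute values.

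The article does not state the points per item, mention a second PPQ version, or give a reason for the different thresholds. Table 3 lists the PPQ under the secondary aims.

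**The concern.** Two things conflict. First, the rule for calling a mother highly stressed is strict (above 6) in one place and inclusive (6 or above) in the other. Both rules are written out in words, so a symbol lost in typesetting does not explain the difference. Second, the response format and the score range in Table 2 cannot both hold under ordinary 0/1 scoring. The reader therefore cannot tell what scale the value 6 sits on.

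The PPQ is the only post-traumatic stress instrument in Table 2, and the emotional state of parents is part of the second hypothesis in the Introduction. Because the PPQ enters the models only through the cut, the cut decides all the information it contributes. With two thresholds in print and tests at 0.05, the choice between them could also be made after the results are seen.

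**Working it through.** **Inputs.** From Table 2: 14 items, yes/no answers, stated range 0–42, high risk above 6. From Statistical analysis design: factor coded at 6 or above. From Sample size calculation: "the number of children with complete analyzable data is estimated at 63 in total". This last figure is used only to scale the effect; 83 × 0.75 = 62.25, which agrees with the stated 63 to within rounding. Infants are singletons, so one mother per child is assumed.

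**Step 1: the range.** Maximum = number of items × maximum points per item.

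- Yes/no at one point per yes: 14 × 1 = 14, so the range is 0–14. The stated 0–42 is not reproduced.
- Points per item needed to reach 42: 42 / 14 = 3. That means either graded items scored 0–3, which contradicts the yes/no format, or 3 points per yes, which is stated nowhere and would allow only multiples of 3.

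**Step 2: what a cut at 6 means on each scale.**

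- 0–14: 6/14 = 43% of the maximum, that is, six yes answers.
- 0–42: 6/42 = 14% of the maximum. On graded 0–3 items, two items at full score reach it.

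**Step 3: the two cut-offs.** On an integer score, above 6 means 7 or more. The two rules disagree for a score of exactly 6 and nowhere else.

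**Step 4: how many mothers that could be.** The documents give no PPQ distribution, so every line below rests on an assumption. For 0–14 scoring with independent items and a common probability p of answering yes, the share at exactly 6 is P(X ≥ 6) − P(X ≥ 7), with X binomial (14, p).

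| Assumption | 6 or above | Above 6 | Exactly 6 | Of 63 |
|---|---|---|---|---|
| 0–14, p = 0.1 | 0.1% | 0.0% | 0.1% | 0.1 |
| 0–14, p = 0.2 | 4.4% | 1.2% | 3.2% | 2.0 |
| 0–14, p = 0.3 | 21.9% | 9.3% | 12.6% | 8.0 |
| 0–14, p = 0.4 | 51.4% | 30.8% | 20.7% | 13.0 |
| 0–14, p = 0.5 | 78.8% | 60.5% | 18.3% | 11.5 |
| 0–42, uniform | – | – | 1/43 = 2.3% | 1.5 |

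These are illustrations, not bounds. Under the unstated scoring of 3 points per yes, a score of 6 is exactly two yes answers. At p = 0.2 that share is 25.0%, or 0.25 × 63 ≈ 16 mothers.

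**The case against.** The best defence is that the analysis section gives an operative rule, while the sentence in Table 2 is background on the instrument and is worded cautiously. On that view the variable can be coded as the analysis section says, and the rest is a misprint in a table. The PPQ is also one factor among many, in analyses labelled exploratory, in a pilot study without a power calculation. The article lists factors to be considered and does not fix which of them stay in the multivariate or mixed models.

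Much of this stands, and it limits the point. Three stronger readings are tempting but not supported:

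- **That post-traumatic stress cannot be coded validly.** A usable rule is given. What is missing is a single, consistent definition. The 0–42 range is ruled out only for one point per yes.
- **That mildly symptomatic mothers will be labelled high risk and the association diluted.** This needs both a 0–42 form in use and a cut of 6 that belongs to a yes/no version. The documents establish neither. A yes/no form with a misprinted range fits the text equally well, and then only the score of 6 is in dispute.
- **That the strict cut-off in Table 2 is the right one.** Nothing favours it over the analysis section. Table 2 is a weak anchor: its range is itself in doubt, and it supports the cut-off with reference numbers that the Introduction uses for attachment topics.

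The defence does not remove the conflict itself. Both thresholds, the format and the range are stated in the article and disagree, so this is not detail left to a fuller document.

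**Conclusion.** The point holds as an inconsistency in the definition of one analysis variable. Two facts are certain from the text: the thresholds differ for a score of exactly 6, and 14 yes/no items at one point each give 0–14, not 0–42. Which range and which threshold are right cannot be settled from the documents.

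The size is uncertain. About 1 to 13 of 63 mothers change group under most of the assumptions tried, with almost none if symptoms are rare and somewhat more under 3 points per yes. All of these figures depend on assumed score distributions, and the binomial ones also on independent items. None is a prediction.

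The consequence is limited to one candidate factor in the exploratory models. The ASCT Q-scores, their description at 3 and 5 years, and the sample size do not depend on it. This should be fixed before analysis, but it does not threaten the primary outcome.

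**What to change.** Before analysis:

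1. State which PPQ version is administered and how each item is scored.
2. Correct either the response format or the range in Table 2 so that the two agree.
3. Use one threshold, belonging to that version and with its source, in both Table 2 and Statistical analysis design.
4. Also enter the total PPQ score as a continuous factor, as is already planned for the PSI and AMMI, so that the result does not hinge on the cut. This is an added safeguard and not itself the correction of an error.

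The cost is a few words in two places and one further model term. No new measurement is needed if the version in use is simply described correctly. The article describes PPQ collection prospectively, so it should not be assumed that the item responses already exist. If only yes/no answers are collected, a graded score cannot be reconstructed from them later, which is a reason to settle the version early.

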## Discussion

The study will provide a better understanding of the attachment representations developed by extremely premature infants and the possible association between these attachment representations and maternal mental health, stress, and neurocognitive development. More knowledge and a better understanding could allow for individualized care at an early stage or even interventions from the neonatal period to improve the outcome of these vulnerable newborns.

The study also offers real advantages for the children and families included. An advisory consultation with the LIFT cohort’s usual partners (psychologist, child psychiatrist, etc.) will be offered if mental or interpersonal difficulties come to light during tests performed as part of the study.

The study is registered with ClinicalTrials.gov, identifier: NCT04304846 (retrospectively registered January 11, 2021). URL: https://clinicaltrials.gov/ct2/show/record/NCT04304846.

## Ethics and Dissemination

This study involving human participants qualifies as an interventional study with minimal risks and constraints in accordance with the decree of April 12, 2018 establishing the list of types of study mentioned in part 2 of Article L.1121-1 of the French Public Health Code, as an adapted care package may be offered following the results of the investigations carried out as part of the study.

The study file received a favorable opinion for the implementation of this research on February 18, 2020 - ID-RCB n°: 2019-A03352-55 (Dossier 2-20-007 id6699) 2°HPS. This study has received authorization from the French Data Protection Authority (CNIL) as per n° 920229.

The LIFT cohort received ethical approval from the Commission Nationale de l’Information et des Libertés (No. 851117) (37).

## Ethics Statement

The studies involving human participants were reviewed and approved by ID-RCB no. 2019-A03352-55 (File 2-20-007 id6699) 2°HPS. This study has received authorization from the French Data Protection Authority (CNIL) under no. 920229. Written informed consent to participate in this study was provided by the participants’ legal guardian/next of kin. Written informed consent was obtained from the individual(s), and minor(s)’ legal guardian/next of kin, for the publication of any potentially identifiable images or data included in this article.
